### Sample size

The primary outcome will be overall pain at 3 months. Very large effects (e.g. >7 on a 10 point scale) have been reported for improvement in pain scores for individual patients. People who undergo conventional treatment will also tend to have some improvement as some acute symptoms subside. To detect a large (i.e. at least a 2.5 unit) advantage of vertebroplasty over placebo in pain score (SD = 3.0, α = 0.05, β = 0.80, 2-tailed t-test) we would require only 24 participants per group. At 12 and 24 months we expect smaller differences to exist between the groups due to the natural course of the disease (i.e. improvements in the placebo group and likely adjustment to the illness) and *possibly *a greater frequency of vertebral fracture in the vertebroplasty group. Using the same assumptions as above but considering a 15% advantage in the vertebroplasty group (mean vertebroplasty improvement = 4.0 units, mean placebo improvement = 2.5 units) we would require 64 people in each group.

The most relevant adverse event from vertebroplasty may be further vertebral fractures. A reasonable estimate for the one year incidence of new fractures in women with at least one fracture and not on preventive treatment is about 20% based on new vertebral fractures observed in the first year for the placebo arm of four risedronate clinical trials [21]. Many participants in our trial are likely to be on treatment for osteoporosis, which may theoretically reduce the risk of further vertebral fracture by 50% to around 10% [21,40,41]. In the two controlled before-after studies there was between a zero and 3 fold increase in the 1 year new fracture risk [42,20]. The risk of fracture in the second year is unknown but likely to be less than in the first year. With 82 people in each group we will have 80% power to detect a 3-fold excess in fractures in the vertebroplasty group (alpha = 0.05, 2-tailed Log rank test). While this study is not specifically designed to assess small group differences related to infrequent events, if medium to large excesses in adverse events are present, the study is adequately powered.

Health-related Quality of Life (AQoL utility score) is an important global secondary outcome at 2 years. This is a complex mix of benefits such as vertebral-specific reduction in pain and decreased distress, but may also involve adverse events such as vertebral re-fracture or hip fracture. The AQoL is an ideal generic instrument to capture broad health-related changes – incorporating a mix of health declines and improvements. With a sample size of 82, there will be 80% power to detect a 0.13 change in Health -related Quality of Life (utility). For example, the improvement in the placebo group may be 0.10 units compared with 0.23 in the vertebroplasty group (sd = 0.3, α = 0.05, 2-tailed t-test). Compared with the disease-specific outcomes noted above, this magnitude of change can be regarded as relatively small but clinically relevant [43]; hence the study is powered to detect even modest overall benefits of vertebroplasty. To allow for attrition, we will increase the sample by 20% to 100 patients per group.

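### Adequate power is claimed for medium excesses in adverse events, but it was calculated only for a 3-fold fracture excess at about a 10% control risk

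*Protocol article*

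**What the plan says.** All the relevant text is in the Sample size section of the protocol article. It treats further vertebral fracture as the most relevant harm and gives two one-year control risks:

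- Without preventive treatment: "the one year incidence of new fractures in women with at least one fracture and not on preventive treatment is about 20" per cent.
- With treatment, which many participants are expected to be taking and which may in theory "reduce the risk of further vertebral fracture by 50% to around 10" per cent.

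On the size of any excess, it reports that in the two earlier controlled studies "there was between a zero and 3 fold increase in the 1 year new fracture risk". On the second year it says: "The risk of fracture in the second year is unknown but likely to be less than in the first year".

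The one power statement is: "With 82 people in each group we will have 80% power to detect a 3-fold excess in fractures in the vertebroplasty group". The error rate and test behind it are given as "alpha = 0.05, 2-tailed Log rank test". The section then allows that "this study is not specifically designed to assess small group differences related to infrequent events", and concludes: "if medium to large excesses in adverse events are present, the study is adequately powered".

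**The concern.** The concluding sentence widens the calculation in two directions without any figure. It goes from a 3-fold excess down to a medium one, and from fractures to adverse events in general. Whatever medium means, it must cover something below large, and 3-fold is already the largest increase the section cites.

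The second aim of the trial is longer-term safety, in particular the excess fracture risk over two years. A published statement of adequate power invites readers to take a non-significant fracture or adverse-event comparison as evidence against a medium excess. Whether that inference is fair depends on a power the plan never calculated.

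**Working it through.** **Inputs from the Sample size section.** 82 evaluable per group, two-sided alpha 0.05, log-rank test, one-year control risk about 10% (treated) or about 20% (untreated). **Assumptions made here.** A 15% control risk as an intermediate value, and 5% for a rarer adverse event.

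**Formulas.** With control risk p1 and vertebroplasty risk p2, expected events are D = 82 × (p1 + p2).

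- Freedman: power = Φ(√D × (HR − 1)/(HR + 1) − 1.96)
- Schoenfeld: power = Φ(½√D × ln HR − 1.96)

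The plan does not say what an r-fold excess refers to, so three readings are shown:

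- (a) hazard ratio r, so p2 = 1 − (1 − p1)^r
- (b) risk ratio r, so p2 = r × p1, with r itself entered as HR
- (c) risk ratio r, with HR = ln(1 − p2)/ln(1 − p1)

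**Reproducing the plan's figure.** Freedman's required events for a ratio of 3 are (1.960 + 0.842)² × (4/2)² = 31.4, so 32. At 10% versus 30% this is 32/(0.10 + 0.30) = 80 per group, against the stated 82. Power at 82 is 81.7% on that reading, and 78.8% for a hazard ratio of 3 (10% versus 27.1%). A 20% control risk would give 96–100% and a 5% risk 51–65%. The stated 80% therefore rests on a control risk of about 10%.

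**Two substitutions for a doubling at 10%.**

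- Hazard ratio 2: p2 = 1 − 0.9² = 0.19, D = 82 × 0.29 = 23.78. Freedman: Φ(4.876 × 1/3 − 1.96) = Φ(−0.334) = 36.9%.
- 10% versus 20%, converted HR = 2.118: D = 82 × 0.30 = 24.6. Schoenfeld: Φ(½ × 4.960 × 0.750 − 1.96) = Φ(−0.099) = 46.1%.

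**Results (power in %, Freedman / Schoenfeld).**

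| Control risk | Excess | (a) | (b) | (c) |
|---|---|---|---|---|
| 10% | 3-fold | 78.8 / 85.8 | 81.7 / 88.2 | 87.6 / 93.7 |
| 10% | 2.5-fold | 60.8 / 66.6 | 63.2 / 68.9 | 70.0 / 76.7 |
| 10% | 2-fold | 36.9 / 39.4 | 38.0 / 40.5 | 42.8 / 46.1 |
| 15% (assumed) | 2-fold | 50.5 / 53.7 | 52.6 / 55.8 | 62.2 / 66.5 |
| 20% | 2-fold | 61.7 / 65.1 | 64.7 / 68.1 | 78.5 / 82.8 |
| 5% (assumed) | 3-fold | 51.1 / 58.8 | 52.6 / 60.4 | 55.8 / 64.6 |

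A simulated log-rank test at 10% control risk gave 37% for a hazard ratio of 2 and 43% for 10% versus 20%, in line with the table. At 10% and 82 per group, the smallest risk ratio with 80% power is about 2.7 to 2.95, depending on the method.

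**The case against.** **The 3-fold figure is right.** This stands. A reader might infer that the 80% is itself miscalculated, since some formulas give 86–94%. The documents do not support that: Freedman's method gives 79–82% on readings (a) and (b).

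**Medium is never defined, and the plan does not claim to detect a doubling.** Also true; a doubling is used here only as an illustration. But a 2.5-fold excess also falls short of 80% at the control risk on which the 82 rests.

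**10% is not the trial-wide risk.** This stands and matters. It is the plan's figure for treated patients. Only many, not all, participants are expected to be treated, and osteoporosis management is left to treating physicians. The aim also runs to two years, which adds events. A reader might infer that the trial would miss a doubling more often than not. That holds at 10%, but not at the 15–20% risks examined, where power is 51–83%. Nor is 19% (1 − 0.9²) a ceiling for two-year risk, because untreated patients reach about 20% in the first year alone. At an assumed 27.75% (15% a year for two years, 1 − 0.85²), a doubling has 94–97% power on reading (c) but 75–78% as a hazard ratio of 2. A 2.5-fold excess has 77–94% at 15% and 87–99% at 20%. The claim might therefore be defensible for some medium excess at some higher risk, but the plan makes neither assumption.

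**100 per group are randomised.** The additional patients are there for attrition. With none lost, a doubling at 10% still has only 43–54%.

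**The plan already hedges.** It disclaims small differences in infrequent events. That does not cover a medium excess in fractures, or a 3-fold excess in a rarer event.

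**Conclusion.** The concern holds as a claim wider than its calculation. The stated power for a 3-fold fracture excess is sound at a control risk of about 10%. The extension to medium excesses, and to adverse events generally, is unsupported. On the basis that yields the plan's own 80%, power is about 61–77% for a 2.5-fold excess and 37–46% for a doubling. At a cumulative control risk of 15–20% a doubling has about 51–83%. It reaches 80% dependably only at higher assumed risks and when read as a risk ratio. At an assumed 5% control risk, even a 3-fold excess has about 51–65%.

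These figures rest on 82 evaluable per group, a two-sided 0.05 log-rank test, and the listed control risks. The second-year risk is not quantified in the plan, so no single two-year power can be given. Sample size, endpoints and analysis are unaffected.

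**What to change.** Replace the concluding sentence with one limited to what was calculated, for example:

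> At a control risk of about 10%, 82 per group gives about 80% power for a 3-fold excess in fractures and about 37–46% for a doubling (about 51–83% if the cumulative control risk is 15–20%). Smaller excesses, and excesses in rarer adverse events, cannot be excluded by a non-significant result.

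State the control risk and time horizon behind the 80%, and whether 3-fold means a hazard ratio or a risk ratio; once these and the formula are fixed, the ranges reduce to single figures. If the word medium is kept, define it and give its power. The change is to wording only and needs no extra patients. Its cost is a less favourable stated power.

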### Planned statistical analysis

Treatment groups will be examined for comparability at baseline with respect to demographic and prognostic factors. An intention-to-treat analysis will be performed using efficacy measures. Simple changes from baseline will be assessed at each time point using t-tests or corresponding nonparametric tests. Analysis of covariance will be applied to assess differences in the 3-month endpoints between groups after adjusting for baseline outcome values and other characteristics imbalanced at baseline if required. Standard regression assumptions will be assessed using diagnostic plots. Repeated measures analysis using linear mixed models will include the 1-week, 1, 3, 6, 12 and 24-month outcomes and will assess constancy of the vertebroplasty effect over time.

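### Baseline adjustment is stated only for the 3-month ANCOVA; the planned change-from-baseline tests at every visit are valid but less efficient than a baseline-adjusted comparison

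*Protocol article*

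**What the plan says.** All three analyses are described in the Planned statistical analysis section of the protocol article.

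- **Change scores, every visit:** "Simple changes from baseline will be assessed at each time point using t-tests or corresponding nonparametric tests".
- **ANCOVA, 3 months only:** "Analysis of covariance will be applied to assess differences in the 3-month endpoints between groups". It adjusts for the baseline value of the outcome and, if needed, for characteristics found to be imbalanced.
- **Linear mixed model, all six follow-ups (1 week to 24 months):** its stated purpose is to see whether the treatment effect stays constant. No baseline covariate is mentioned for it.

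The Sample size section fixes the endpoint: "The primary outcome will be overall pain at 3 months". It sizes later pain and AQoL by two-tailed t-tests on group differences in mean improvement. The Randomisation section stratifies by treating radiologist, gender and symptom duration. The analysis section does not mention these strata.

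**The concern.** Baseline values of pain, disability and quality of life are collected for everyone, yet the plan states their use as a covariate at one visit only. At every visit it writes in a test that subtracts the baseline. Subtraction gives the baseline a fixed coefficient of 1. When baseline and follow-up are only moderately correlated, this adds baseline noise to the comparison and handles chance baseline imbalance less well than conditioning on baseline does.

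What is at stake is precision for the secondary and later comparisons. One of these is AQoL at 2 years, which the Sample size section presents as an important global outcome and for which the planned number gives only about 80% power. A lesser issue is that the extra ANCOVA covariates depend on the imbalance observed, so the adjusted 3-month result is not fully fixed in advance.

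**Working it through.** **Inputs (Sample size section)**
- Primary pain effect: 2.5 units, SD 3.0, two-sided 0.05, 24 per group: "SD = 3.0, α = 0.05, β = 0.80, 2-tailed t-test) we would require only 24 participants per group". The printed β of 0.80 must mean power, since 24 reproduces only on that reading.
- Pain at 12 and 24 months: 4.0 − 2.5 = 1.5 units, 64 per group.
- AQoL: "the improvement in the placebo group may be 0.10 units compared with 0.23 in the vertebroplasty group (sd = 0.3, α = 0.05, 2-tailed t-test", that is 0.13 units, with 82 per group before the attrition allowance.
- The correlation r between baseline and follow-up is not given, so a range is used.

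**Step 1: the plan's own figures**
- 2.5 units, SD 3.0: the exact t-test solution is 23.6, so 24. Reproduced.
- 1.5 units, SD 3.0: 63.8, so 64. Reproduced.
- 0.13 units, SD 0.3, n = 82: SE = 0.3 × √(2/82) = 0.0469, and 0.13/0.0469 = 2.775. Power = Φ(2.775 − 1.960) = 79.2% (78.8% with the t distribution), close to the stated 80%.

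The sample size is therefore not at fault.

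**Step 2: efficiency of the two methods**

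Assume the same SD s at baseline and follow-up.
- Change score: variance = 2(1 − r)s².
- ANCOVA: variance = (1 − r²)s².
- Ratio ANCOVA/change = (1 − r²)/[2(1 − r)] = (1 + r)/2.

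**Step 3: effect on AQoL at 82 per group**

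Take 0.3 as the SD of change. The adjusted SD is 0.3 × √((1 + r)/2), and power = Φ(0.13/SE − 1.960) with SE = SD × √(2/82).

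| r | Variance ratio | Variance cut | Adjusted SD | SE | Power |
|---|---|---|---|---|---|
| change score | 1 | – | 0.300 | 0.0469 | 79.2% |
| 0.2 | 0.60 | 40% | 0.232 | 0.0363 | 94.8% |
| 0.5 | 0.75 | 25% | 0.260 | 0.0406 | 89.3% |
| 0.7 | 0.85 | 15% | 0.277 | 0.0432 | 85.3% |
| 0.9 | 0.95 | 5% | 0.292 | 0.0457 | 81.2% |

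**Step 4: effect on pain at 82 per group**
- 1.5 units, with 3.0 as the SD of change: 89.3% with the change score; with ANCOVA 98.5% (r = 0.2), 95.9% (0.5), 93.5% (0.7) or 90.7% (0.9).
- 1.5 units, with 3.0 as the SD of the score itself and r = 0.3: the change SD is 3.0 × √1.4 = 3.55, giving 77.2%; the ANCOVA SD is 3.0 × √0.91 = 2.86, giving 91.9%.
- 2.5 units, with 3.0 as the SD of change: SE = 3.0 × √(2/82) = 0.469, and 2.5/0.469 = 5.34. Power exceeds 99.9% with the change score alone.

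**The case against.** The strongest reply is that the plan already has a mixed model over all six follow-ups. A reader might infer that the change-score test is the only group comparison outside 3 months. The document does not support that, because the mixed model compares groups at those same visits. What stands is narrower: baseline adjustment is stated for 3 months only.

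Second, the change-score sentence does not say that it compares groups, and it could be a preliminary summary. A between-group test is the more natural reading, because the Sample size section applies t-tests to differences in improvement, but it remains an inference.

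Third, a reader might infer competing primary tests and an inflated type I error. If either the change-score test or the ANCOVA could be declared the 3-month result, 20,000 simulated null trials of 82 per group gave about 8.1% (r = 0.2) to 6.9% (r = 0.7). That assumes free choice between the tests, which the document nowhere allows. The primary outcome and time point are fixed, the ANCOVA is aimed at 3 months, and ranking of analyses commonly sits in an analysis plan that is not shown.

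Fourth, loss of participants with a missed visit does not separate the methods. A 3-month ANCOVA loses them too, and the mixed model can use the visits available.

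Finally, change scores are valid under randomisation and match the plan's own sizing. Both points are correct. They answer a charge of bias but not one of inefficiency.

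**Conclusion.** The point holds as one of efficiency. The plan writes in a change-score test at every visit and states baseline adjustment at one visit only, although the baseline data are already collected and a model for all visits is already planned. For any r below 1 the adjusted comparison is more precise, with a variance cut of 5% to 40% for r from 0.9 to 0.2.

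For AQoL at 2 years this means roughly 85% to 95% power instead of 79% (r from 0.7 to 0.2), and only about 81% at r = 0.9. For the 2.5-unit primary effect the gain has no practical weight.

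These figures assume equal SDs at baseline and follow-up, 0.3 as the SD of AQoL change, 82 evaluable per group and a normal approximation. Because r is unknown, no single gain should be claimed. The point does not show bias, an invalid test, an inadequate sample size or an inflated error rate.

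**What to change.** Reword the Planned statistical analysis section as follows.

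1. Report changes from baseline by group as description only, without t-tests or nonparametric tests.
2. Add to the planned linear mixed model the baseline value of the outcome, by time, and the randomisation strata (treating radiologist, gender, symptom duration) as prespecified covariates. Read the group contrast at each of the six follow-ups from this model.
3. Name one primary test: this model's 3-month contrast for overall pain. Keep the 3-month ANCOVA as a supportive analysis with the same prespecified covariates, in place of covariates chosen by observed imbalance. The two should not be called equivalent, because they generally differ when visits are missing.

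The cost is rewording. No further data, visits or participants are needed.

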### Randomisation

Participants who fulfil inclusion criteria and consent to take part in the trial will be randomised in permuted blocks of 4 and 6, stratified by treating radiologist, gender and duration of symptoms (< 6 weeks versus = 6 weeks), to receive either the active or placebo regimen according to a computer-generated table of random numbers created by the study biostatistician. To ensure treatment allocation concealment, just prior to the procedure the treating radiologist contacts a central receptionist who provides the appropriate opaque sealed envelope containing the treatment allocation of the participant according to their identification number. Only the telephone receptionist has access to the allocation schedule and she has no other role in the trial.

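### Covariates for the 3-month pain analysis are to be chosen from observed baseline imbalance, a rule that will rarely select the randomisation strata, which no analysis names

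*Protocol article*

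**What the plan says.** All references are to the protocol article.

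- **Sample size:** "The primary outcome will be overall pain at 3 months".
- **Randomisation:** allocation is in permuted blocks of 4 and 6, "stratified by treating radiologist, gender and duration of symptoms" (under 6 weeks or longer).
- **Planned statistical analysis:** the groups are first compared at baseline. Three analyses follow: t-tests (or nonparametric tests) on change at each time point, analysis of covariance for the 3-month endpoints, and linear mixed models over all follow-up times. The analysis of covariance is done "after adjusting for baseline outcome values and other characteristics imbalanced at baseline if required".

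The section gives no list of candidate characteristics, no criterion for imbalance and no meaning for the closing condition. It does not call any of the three analyses primary, and it names the stratification factors in none of them.

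**The concern.** Two things follow from the stated rule.

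First, the model for the primary endpoint is settled only after the groups have been compared. Under randomisation a baseline imbalance is a chance event. What makes a covariate worth including is how strongly it predicts the outcome, not whether it happens to differ between arms. Without a list or a criterion, several models are open to the analyst, and a critic can question whichever one is reported.

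Second, the rule works against the covariates that the design singles out. Stratified blocking exists to keep radiologist, gender and duration balanced, so they will seldom look imbalanced. Yet if they predict pain, the analysis has to include them for the standard error to reflect the balance that was achieved. The article itself gives reason to think duration matters: the Background says the condition tends to improve with time and that results in patients treated early may not carry over to longer-standing pain.

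At stake are the width of the confidence interval and the credibility of the model. Both matter in a trial whose Discussion expects a finding of no benefit over placebo to affect practice.

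**Working it through.** **1. The plan's own figures.** Inputs from Sample size: "SD = 3.0, α = 0.05, β = 0.80, 2-tailed t-test" (0.80 is the power, although printed as β); a difference of "at least a 2.5 unit"; and, for later time points, "mean vertebroplasty improvement = 4.0 units, mean placebo improvement = 2.5 units", a difference of 1.5.

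Normal approximation, n per group = 2·SD²·(1.960 + 0.842)²/δ²:
- δ = 2.5: 2 × 9 × 7.85 / 6.25 = 22.6, so 23. The exact t-test gives 23.60, so 24.
- δ = 1.5: 2 × 9 × 7.85 / 2.25 = 62.8, so 63. The exact t-test gives 63.77, so 64.

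The article states "we would require only 24 participants per group" and "we would require 64 people in each group". Both reproduce, and neither depends on the covariate rule.

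**2. Expected size under perfect balance.** Let ρ be the correlation of baseline with 3-month pain and R² the share of 3-month pain variance explained by the strata. A model with baseline pain but no strata overstates the standard error by about √[(1 − ρ²)/(1 − ρ² − R²)]. With ρ = 0.4 (assumed):
- R² 0.05: √(0.84/0.79) = 1.03
- R² 0.10: √(0.84/0.74) = 1.07
- R² 0.20: √(0.84/0.64) = 1.15

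Balance is not perfect, because blocks are left incomplete in small strata, so the real figures should be somewhat lower.

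**3. Simulation.** Stratified permuted blocks of 4 and 6 were simulated with 4000 runs per scenario. Assumptions not in the document: 164 evaluable participants (2 × 82), 4 radiologists, 20% men, 40% under 6 weeks, ρ = 0.4, and 8 further covariates explaining 20% of variance. Each cell gives model SE divided by true SE, then two-sided type I error.

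| Strata R² | Baseline pain only | Baseline pain plus covariates with p<0.05 for imbalance | Baseline pain plus strata |
|---|---|---|---|
| 0 | 0.97; 5.5% | 1.00; 4.7% | 0.97; 5.6% |
| 0.05 | 1.03; 4.5% | 1.05; 4.1% | 1.00; 4.9% |
| 0.10 | 1.03; 4.5% | 1.07; 3.8% | 0.98; 6.0% |
| 0.20 | 1.09; 3.4% | 1.14; 2.5% | 0.97; 5.6% |
| 0.30 | 1.21; 1.5% | 1.26; 1.2% | 1.02; 4.7% |

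The p<0.05 criterion is the simulation's, not the document's.

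The simulation margin is about ±0.7 points on an error rate (1.96 × √(0.05 × 0.95/4000)) and about ±2% on a ratio (1.96/√8000). Separate runs at a true effect of 1.5 gave 1.04 and 1.12 for baseline only at R² 0.10 and 0.20. Because of that spread, the first and last models were rerun with 30,000 runs under the same assumptions. Baseline only gave 1.03, 1.05 and 1.12 at R² 0.05, 0.10 and 0.20, with type I error 4.3%, 3.8% and 2.8%. With the strata included, the ratio was 0.99 to 1.00 and type I error 4.7% to 5.1%. The 4000-run figures at 0.10 and 0.20 are therefore at the low end, and ranges are quoted below.

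**4. Power at 1.5 units, 82 per group.**
- R² 0.10: 95.0% with strata, 93.8% without, a loss of 1.2 points.
- R² 0.20: 97.8% with strata, 95.5% without, a loss of 2.3 points.

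**5. Free choice of covariates.** Suppose the analyst keeps the most favourable of three models: baseline only, selection at p<0.05, or selection at p<0.10. Type I error is then 6.3% at R² 0, 5.5% at 0.05 and 5.3% at 0.10. At a true effect of 1.5 units the estimate is overstated by about 0.05 units. Part of the 6.3% is simulation error, since the fixed baseline-only model ran at 5.5% in the same scenario.

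**The case against.** The strongest reply is that this is a one-paragraph analysis section in a journal article. A covariate list is commonly left to the analysis plan, and not naming the strata is not a decision to exclude them. That is right as far as it goes: silence on the strata alone would not be a finding. But the article is not silent on how covariates are chosen. It states a rule based on imbalance, and an analysis plan could mend that only by departing from the published sentence.

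The effects are also small, and that stands. For the 2.5-unit difference planned at 3 months, 82 per group gives more than 99.9% power even with an unadjusted t-test, so lost power does not threaten the primary comparison.

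A reader might infer more than the text supports:

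- *That the primary model itself is shown to be wrong.* No analysis is labelled primary. That the analysis of covariance plays this part is inferred from the 3-month outcome, and t-tests on change are listed for the same time point. Those do not name the strata either.
- *That the standard error is certainly misstated.* It is so only if the strata predict 3-month pain; at R² of zero there is no such effect.
- *That there is about an even chance of chance imbalance altering the model.* Counting 13 baseline characteristics, each tested at 5%, gives 1 − 0.95¹³ = 49%. The article states no such test. The characteristics are unlikely to be independent. The count appears to include gender, which is a stratum. An imbalance need not lead to adjustment under the stated condition. The figure should not be used.

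**Conclusion.** The point holds in a limited form. The covariate rule for the 3-month endpoints depends on the observed data, and it is stated, not merely left open. It will rarely select the stratification factors; incomplete blocks make rarely a fairer word than never.

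The consequences run in two directions, both modest:

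- **Strata omitted:** if they explain 5%, 10% or 20% of 3-month pain variance, the standard error from the model with baseline pain only is too large by about 3%, 3 to 5%, or 9 to 12%. Type I error falls from about 4.5% to about 3% across that range, and power drops by one to two points. This makes the test conservative and does not create false positives.
- **Covariates freely chosen:** type I error could rise to about 6% at most in these simulations.

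The sizes rest on assumed values for R², the baseline correlation, the number of radiologists and the mix of participants, none of which the document gives. The planned sample size stands. The change is worth making because it removes an avoidable challenge to the main result at almost no cost.

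**What to change.** Replace the imbalance rule with a named model: the primary analysis is an analysis of covariance of 3-month overall pain on treatment, baseline pain, symptom duration (under 6 weeks or 6 weeks and longer), gender and treating radiologist, with low-volume radiologists pooled or fitted as a random effect. Use the same covariates in the linear mixed model. Put any further adjustment into a sensitivity analysis whose covariates are named before unblinding, on prognostic grounds and not on observed imbalance.

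The cost is one sentence and a few degrees of freedom: with four radiologists as fixed effects, 3 + 1 + 1 = 5. All the variables are already collected.
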